## Abstract

**Background:**

Out-of-hospital cardiac arrest (OHCA) is a time-sensitive emergency associated with high mortality and substantial risk of neurological disability. Extracorporeal cardiopulmonary resuscitation (ECPR) using extracorporeal membrane oxygenation (ECMO) has been introduced for refractory cardiac arrest, but recent randomized controlled trials have reported conflicting results, and the benefit of ECPR implemented according to rigorously timed protocols remains uncertain.

**Aim:**

This trial evaluates whether emergency total extracorporeal life support (ECLS), with emphasis on expedited cannulation and active left ventricular (LV) unloading, improves 30-day survival with favourable neurological outcome compared with standard advanced cardiac life support (ACLS) with rescue ECLS in adults with refractory shockable out-of-hospital cardiac arrest.

**Design, setting, and participants:**

This is a prospective, investigator-initiated, multicenter, open-label randomized clinical trial conducted in eight experienced extracorporeal membrane oxygenation (ECMO) centers in the Taipei metropolitan area. Eligible adults aged 18–75 years with witnessed refractory shockable OHCA (ventricular fibrillation or pulseless ventricular tachycardia) who received bystander cardiopulmonary resuscitation (CPR) are randomized 1:1 on emergency department (ED) arrival.

**Interventions:**

Participants are assigned to: (1) emergency total ECLS, with initiation as soon as possible after randomization and within 60 min of the emergency call, or (2) standard ACLS with rescue ECLS, in which at least 15 min of standard ACLS is provided in the ED before ECLS is considered. Both groups receive immediate coronary angiography and percutaneous coronary intervention (PCI) when indicated, and active LV unloading is recommended according to prespecified criteria.

**Primary endpoint:**

Survival at 30 days with favorable neurological status, defined as a Cerebral Performance Category score of 1 or 2.

**Conclusion:**

The ECLS-OHCA trial will provide complementary randomized evidence on the impact of expedited time-to-flow and protocolized LV unloading on neurological outcomes in refractory shockable OHCA and will explore the cost-effectiveness of this strategy.

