### Novelty

Our protocol is designed to address this by incorporating active LV unloading strategies under prespecified criteria (see below). Early active LV unloading during ECMO support improves survival in patients with cardiogenic shock, and concomitant LV unloading has been associated with favorable outcomes in refractory cardiac arrest. We incorporate the concept into the ECPR to validate its efficacy. The estimated call to ECMO perfusion may be expected longer than previous studies since we allowed emergency call to ED within 60 min.

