### Enrollment and randomization of trial population

Refractory OHCA is defined as cardiac arrest in patients transported to hospital with ongoing CPR. Upon receiving the EMS’s referral of OHCA patients, the OHCA response team, composed of emergency physicians, interventional cardiologists, and cardiac surgeons, will evaluate the eligibility of patients based on on-scene information. The inclusion and exclusion criteria are described in Table 1. When the patient arrives at the ED, a rapid screening is performed to reassure his/her eligibility. All eligible patients will be randomized into the emergency total extracorporeal life support (total ECLS) group and the standard advanced cardiac life support with rescue ECMO (**standard ACLS**) group (Fig. 1).

**Table 1 Tab1:** PreInclusion and exclusion criteria

Screening inclusion criteria	Pre randomization Exclusion	Post-randomization exclusions criteria
• Aged 18–75 years old	• Age under 18 or over 75	• Age < 18 years or > 75 years old
• Witnessed cardiac arrest with bystander cardiopulmonary resuscitation	• Major trauma	• Initial non-shockable rhythm, i.e. pulseless electrical activity or asystole
• Initial shockable rhythm, i.e. ventricular fibrillation or pulseless ventricular tachycardia	• Initial non-shockable rhythm	• Acute aortic dissection
• Need for repeated defibrillation shocks (> 2) by external defibrillator	• Major trauma	• Acute massive pulmonary embolism
• Estimated transportation time from activation of the emergency response system to arrival at emergency department of participant institutions less than 60 min	• Suicide, illicit drug overdose or intoxication	• Acute intracerebral hemorrhage
	• Pre-arrest mRS > 3 or CPC > 2	• Major trauma due to blunt, penetrating or burn injury
	• Unwitnessed CPR	• Severe peripheral artery disease
		• Known pregnancy
		• Suicide, illicit drug overdose or intoxication
		• Known pre-arrest mRS > 3 or CPC > 2
		• Active malignancy with a life expectancy of less than 1 year
		• Effective DNR order
		• Absolute contraindications to emergency coronary angiography, including known anaphylactic reaction to angiographic contrast media, acute bleeding

CPC, cerebral performance category; DNR, do-not-resuscitation; mRS, modified Rankin score

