**Fig. 1 Fig1:**
[figure not shown]
Study flowchart. Before arriving at ED, the eligibility of OHCA patients will be evaluated by the OHCA response team of the receiving hospital, based on on-scene information provided by EMS. For eligible OHCA patients, randomization will be completed within 5 min of arrival at ED. After CT imaging, patients of first enrollment will be checked again if any exclusion criteria are met. Only patients who received early coronary angiography and/or intervention will be included in the final analysis. ACLS: advanced cardiovascular life support; CCL: cardiac catheterization laboratory; CPC: cerebral performance category; CPR: cardiopulmonary resuscitation; CT: computed tomography; ECLS: extracorporeal life support; ED: emergency department; EKG: electrocardiography; EMS: emergency medical services; mRS: modified Rankin scale; OHCA: out-of-hospital cardiac arrest; ROSC: return of spontaneous circulation; ECG: echocardiography

Randomization is performed immediately upon ED arrival (target: within 5 min) for patients meeting inclusion criteria and experiencing refractory cardiac arrest (defined as ongoing CPR on arrival). Patients with stable ROSC before randomization (defined as sustained pulse with systolic BP ≥ 90 mmHg without ongoing chest compressions for ≥ 2 min) are not randomized and proceed directly to coronary angiography.

Patients with unstable ROSC defined as: (1) return of pulse but requiring ongoing chest compressions, (2) recurrent VF/VT requiring repeated defibrillation, (3) persistent profound hypotension with systolic BP < 90 mmHg or mean BP < 60 mmHg despite vasopressor support, or (4) intermittent epinephrine injection to maintain the heart beating are eligible for randomization."

A computerized randomization list is provided by the National Taiwan University Hospital Clinical Trial Center by a software app (REDCAP). The randomization is in 1:1 ratio, stratified by participant hospitals, with a permuted block of 4. In-hospital randomization is conducted by OHCA response team coordinators immediately after the eligible patients arrive at ED. The randomization codes will be maintained by the National Taiwan University Hospital Clinical Trial Center and monitored by the Data Safety Monitoring Committee. The EMS teams and intensivists in the cardiac intensive care unit (ICU) will be blinded to the study group assignment and follow the institutional standards for post-cardiac arrest care.

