#### LV unloading in ECMO-supported patients

During ECMO support, active left ventricular (LV) unloading by balloon atrial septostomy, direct left atrial venoarterial (LAVA) cannulation, Impella®, percutaneous LV/pulmonary artery venting, would be considered when LV global akinesia, absence of aortic valve opening, or spontaneous echocardiographic contrast within LV is demonstrated by echocardiography, or frothy sputum with pulmonary congestion is present, or pulse pressure < 10 mmHg, or elevated left ventricular end-diastolic pressure $$\ge$$ 30 mmHg (Table 2).

**Table 2 Tab2:** Criteria and indications for active left ventricular (LV) unloading

1. Persistent refractory VF/VT even after ECMO
2. Non-opening aortic valve
3. Pulse pressure < 10 mmHg
4. Severe LV dilatation/global hypokinesia
5. Severe pulmonary edema with frothy sputum
6. LVEDP $$\ge$$ 30 mmHg
7. “Smoke” image in LV, spontaneous echocardiographic contrast

ECMO: extracorporeal membrane oxygenation; LV: left ventricle; LVEDP: left ventricular end-diastolic pressure; VF: ventricular fibrillation, VT: ventricular tachycardia

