## Conclusion

The ECLS-OHCA trial is a multicenter, open-label, interventional randomized clinical trial conducted in a metropolitan area with a well-developed EMS system and densely distributed healthcare facilities. All participating institutions are expert ECMO centers capable of 24/7 ECMO cannulation and transportation, allowing for expedited application of ECPR in eligible candidates with refractory shockable OHCA. Patients without identified noncardiac causes of OHCA will receive immediate CAG and primary PCI if indicated. Institutional protocols of post-cardiac arrest care will adhere to established recommendations from the latest guidelines. Active LV unloading is suggested in cases demonstrating the signs of LV overload. Our trial aims to provide complementary evidence supporting the use of ECPR in refractory shockable OHCA and to assess the cost-effectiveness of its early implementation.

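### The abstract and the Novelty section claim randomised evidence on LV unloading, but unloading follows the same criteria in both arms and is not randomised

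*Protocol article*

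**What the plan says.** Two statements make a claim about unloading itself. The abstract's conclusion says the trial "will provide complementary randomized evidence on the impact of expedited time-to-flow and protocolized LV unloading on neurological outcomes". The Novelty section of the Introduction, after citing benefit from unloading, adds: "We incorporate the concept into the ECPR to validate its efficacy".

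The abstract's Aim describes the experimental strategy "with emphasis on expedited cannulation and active left ventricular (LV) unloading, improves 30-day survival with favourable neurological outcome" and sets it against standard ACLS with rescue ECLS. It does not say that the comparator has the same unloading policy.

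The description of care differs from this:

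- Abstract, Interventions: "Both groups receive immediate coronary angiography and percutaneous coronary intervention (PCI) when indicated, and active LV unloading is recommended according to prespecified criteria".
- LV unloading in ECMO-supported patients: the rule opens "During ECMO support, active left ventricular (LV) unloading by balloon atrial septostomy" and lists further techniques and triggering signs. Neither that text nor Table 2 mentions the arm.
- Final Conclusion: "Active LV unloading is suggested in cases demonstrating the signs of LV overload".

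On allocation, the Enrollment and randomization section says: "All eligible patients will be randomized into the emergency total extracorporeal life support (total ECLS) group and the standard advanced cardiac life support"; this second arm allows ECMO as a rescue. On the method of allocation it adds: "The randomization is in 1:1 ratio, stratified by participant hospitals, with a permuted block of 4".

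**The concern.** A randomised trial gives randomised evidence on what allocation determines. Here allocation determines the ECLS strategy. The abstract nevertheless names unloading beside time-to-flow as a second thing on which randomised evidence will be produced, and the Novelty section speaks of its efficacy.

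The stake is what may be concluded. If the trial is positive, these statements invite readers to take the result as randomised support for invasive unloading procedures. If it is null, they invite the opposite inference. Neither would be warranted.

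**Working it through.** The plan gives no figure for ECMO use or unloading use in either arm, so there is none to reproduce. The check is a comparison of sections, followed by an illustration on assumed values.

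**1. What is randomised.** There is one two-arm factor, allocated 1:1 within hospital. No second factor or stratum concerns unloading.

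**2. Who can be unloaded.** The condition is being on ECMO and showing a listed sign. Under Intervention—ECMO initiation, control patients without stable ROSC after the initial ACLS period can receive rescue VA-ECMO unless it is judged futile. They then come under the same criteria. Unloading is described as considered, recommended or suggested, and never as assigned by arm. The Enrollment and randomization section also has the cardiac ICU intensivists blinded to allocation, so unloading decided there is not meant to differ by arm.

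**3. What the plan compares.**

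| Place | Contrast stated | Unloading in the contrast? |
|---|---|---|
| Knowledge gap, hypothesis | Early ECLS vs conventional ACLS with rescue ECLS | No |
| Table 3, intervention and comparator | Expedited ECPR vs conventional CPR with rescue ECLS, early revascularisation in both | No |
| Statistical analysis, primary model | Treatment group, with centre as covariate | No |
| Subgroup analysis | Age, gender, call-to-ED time, ST elevation, lactate, pH | No |
| Study endpoints | Adverse events related to unloading, as a safety endpoint | Safety only |

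Nothing in the stated analyses could yield the evidence promised in the two claims.

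**4. Could a between-arm difference in unloading rescue the claim?** Let e be the proportion of an arm on ECMO and u the share of those patients who are unloaded, with T for total ECLS and C for control. The difference in unloading use is

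D = e_T·u_T − e_C·u_C = (e_T − e_C)·(u_T + u_C)/2 + (u_T − u_C)·(e_T + e_C)/2.

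The first term comes from ECMO use. The second comes from the share of ECMO patients who are unloaded, which may vary with the timing of ECMO. Both follow from the randomised strategy.

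Illustration (every value is an assumption; none is in the documents):

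- Equal ECMO use and equal share: D = 0.
- ECMO 80% vs 60%, share 30% in both: (0.80 − 0.60) × 0.30 = 0.06.
- ECMO 80% vs 60%, share 50% in both: 0.40 − 0.30 = 0.10.
- ECMO 80% vs 40%, share 70% in both: (0.80 − 0.40) × 0.70 = 0.28.
- ECMO 80% in both, share 70% vs 50%: 0.56 − 0.40 = 0.16. Here the difference arises without any difference in ECMO use.

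If unloading itself added 10 percentage points to favourable survival (also assumed), the second and fourth cases would move the arm difference by 0.06 × 10 = 0.6 and 0.28 × 10 = 2.8 points. The design assumes 25% − 12% = 13 points in total.

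**5. Separability.** Whatever D is, allocation also changes when and whether ECMO flow starts, and that is expected to affect outcome directly. Allocation therefore cannot serve as a stand-in for unloading, and the part of any effect due to unloading cannot be isolated from the arm comparison.

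**The case against.** The best defence is that the abstract's conclusion describes a bundle. Its sentence ends by referring to a single strategy, and a pragmatic strategy trial may describe its package by its components. This fails as a defence of the claim, because the comparator carries the same component under the same criteria, so unloading does not define the contrast. It also does not cover the Novelty sentence, which is about unloading in its own right.

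Other parts of the defence stand:

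- The hypothesis, the primary model and the final Conclusion make no claim about an unloading effect. The problem is confined to two statements.
- The Aim can be read as an accurate description of the care package. It needs clarification, not removal of unloading.
- Presenting protocolised unloading as a feature that earlier trials lacked is legitimate.
- Adverse events related to unloading are already a safety endpoint.

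A reader might infer two stronger points that the documents do not support. One is that unloading can differ between arms only through how many patients receive ECMO. Timing of ECMO also differs by design and could change how many patients show the triggering signs. The other is that the trial plans to compare unloaded with non-unloaded patients. No such analysis is stated. One would be confounded by indication if added later, since the signs mark poor LV function, but that is a caution and not an error in the plan.

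**Conclusion.** The concern holds for the abstract's conclusion and the Novelty section: they state an evidential property that the design does not have. The trial can estimate the effect of emergency ECLS versus standard ACLS with rescue ECLS, given an unloading policy common to both arms. It provides no randomised contrast in unloading.

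This rests on the text alone. The 0 to 28 point range in unloading use and the 0.6 to 2.8 point shift depend on assumed inputs and only show scale; no choice of those inputs would make the unloading effect identifiable.

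A reader might go further and infer that the primary comparison is compromised. It is not: allocation, endpoint and primary model are untouched. The consequence is for what may be concluded, and correction is worthwhile before results are known.

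**What to change.** - In the abstract's conclusion and the Novelty section, limit the claim to the randomised contrast: emergency total ECLS versus standard ACLS with rescue ECLS, under a common policy for LV unloading. Drop the statements that the trial gives randomised evidence on unloading or establishes its efficacy.
- In the abstract's Aim, add that the unloading policy applies to ECMO-supported patients in both arms.
- Report unloading use by arm descriptively, next to the safety events already planned.
- Label any analysis of unloading itself non-randomised and exploratory.

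The cost is rewording and a less ambitious claim. No procedure, clinical criterion, sample size or primary analysis changes.

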**Trial Registration:**

ClinicalTrials.gov: NCT06692075.

**Supplementary Information:**

The online version contains supplementary material available at 10.1186/s13049-026-01557-w.

## Introduction

### Global burden of out-of-hospital cardiac arrest

Out-of-hospital cardiac arrest (OHCA) is a global public health burden, characterized by the high mortality, the potential for long-term disability, and the strain on healthcare systems. The incidence of emergency medical services (EMS)-treated OHCA has been reported as 40.6 per 100,000 person-years in Europe, 47.3 in North America, 45.9 in Asia, and 51.1 in Australia [1]. Hospital survival after OHCA varies substantially by region, and a global survival rate is estimated to be around 8 to 10% [2].

OHCA is a highly time-sensitive medical emergency whose outcome is heavily impacted by prompt resuscitation and intervention before irreversible organ damage develops. Early recognition of OHCA and activation of the emergency response system, and immediate initiation of cardiopulmonary resuscitation (CPR) result in a doubling or even tripling of survival rates of OHCA [3]. For individuals experiencing OHCA with shockable rhythms (e.g., ventricular fibrillation (VF) and pulseless ventricular tachycardia (pVT)), early defibrillation is the key action to further improve the chances of survival [4]. According to the International Liaison Committee on Resuscitation (ILCOR) survey in 2025, survival to hospital discharge or 30-day survival after EMS-treated OHCA and bystander-witnessed shockable OHCA ranged from 3.1% to 20.4% and from 11.7% to 47.4%, respectively [1].

### Extracorporeal cardiopulmonary resuscitation for refractory OHCA

Refractory cardiac arrest, defined as the failure to achieve sustained return of spontaneous circulation (ROSC) despite prolonged CPR efforts or multiple defibrillation attempts, is associated with an even worse prognosis [5]. It is estimated that greater than 70% of patients with shockable OHCA are refractory to conventional CPR and remain pulseless on arrival at the emergency department (ED) [6]. Extracorporeal cardiopulmonary resuscitation (ECPR) is the application of extracorporeal membrane oxygenation (ECMO) or extracorporeal life support (ECLS) in patients with refractory cardiac arrest, aiming to immediately reconstitute the cardiopulmonary function outside patients’ bodies and thus buy time for the delivery of interventions necessary to regain an adequate native circulation [7]. As the most efficient approach of resuscitation for refractory cardiac arrest, the number of ECPR runs has increased tenfold over the last decades [8]. Multiple observational studies have supported the use of ECPR in refractory OHCA [9]. Encouragingly, in expert institutions with highly dedicated and well-trained ECPR teams, a > 40% functionally intact survival of refractory OHCA could be achieved [9, 10]. However, recent randomized controlled trials (RCT) have reported seemingly inconsistent results of ECPR for refractory OHCA [11–13]. Latest update on Adult Advanced Cardiovascular Life Support (ACLS) from the ILCOR Consensus on Science With Treatment Recommendations recommendation assigns a IIa recommendation for use of ECPR in patients with cardiac arrest refractory to standard ACLS [14].

While first responders’ actions are critical to grab the chance of survival in patients with OHCA, studies have shown that the probability of survival with good functional recovery declines rapidly with each minute of CPR surpassing the effective duration, and that repeating the same therapies that did not work during this window did not yield significant survival benefits [15]. To boost the survival without severe impairment in patients with refractory OHCA, efficient strategies to minimize the low-flow duration should be considered. According to the Extracorporeal Life Support Organization guideline, ECPR should be considered after 10–15 min of unsuccessful conventional resuscitation efforts [7]. Observational data suggested that time to ECMO inversely correlated with neurologic outcomes in patients receiving ECPR [16]. In view of the inherent drawbacks of time elapsed in prehospital resuscitation in OHCA, as reflected in three published RCTs (the average interval from emergency calls to ECMO initiation was 59 min, 62 min, and 74 min, respectively), we believe that the benefits of ECPR for refractory OHCA should be investigated in the context of more timely application [17]. The similar result from retrospective data in ECPR also demonstrated 60 min between arrest-to-ECMO was an important factor for better neurological outcome [18].

To add to the evidence on the effectiveness of ECPR for patients with refractory OHCA with longer duration of low-flow time, we propose the present prospective randomized open label clinical trial. The centers are all experienced centers in performing ECPR and coronary intervention and located in the Taipei metropolitan area.

### Knowledge gap

The three recent RCTs [11–13] (ARREST, Prague OHCA, INCEPTION) showed conflicting results. The real answer in this field is debatable. The key limitations of previous trials included single center or limited cases number, or trial in multiple centers with different various experience, lack of standardized post-cardiac arrest care protocols, and absence of systematic LV unloading strategies.

Our trial specifically addresses these gaps by: (1) expedited ECPR with target ≤ 60 min from emergency call to ER, and a 15-min standard ACLS in expert location/team to evaluate standard ACLS in the ECPR setting. (2) standardized post-cardiac arrest care including early coronary angiography, and (3) protocolized active LV unloading.

Our hypothesis is that early initiation of ECLS, compared with conventional ACLS with rescue ECLS, could increase 30-day neurologically favorable survival of patients experiencing refractory OHCA presented with initial shockable rhythm.

